# Administrative Information

## Trial registration

Trial identifier: Request Id: 380316 (submitted to Australian New Zealand Clinical Trials Registry; ANZCTR, not registered yet)

Registry name: web-based stress management intervention for Chinese adolescents in school settings: A randomized controlled trial investigating effect on perceived stress levels

## Funding

There is no funding for this trial.

### Role of study sponsor and funders

The data collected in this study will be stored and managed using the UQ Research Data Manager (UQRDM), which is an online data storage system owned by The University of Queensland, Australia.

# Introduction

## Background and rationale

Adolescence is a transitional period with rapid physical and psychosocial changes, which is a developmental period sensitive to stress (1). It is worth noting that levels of stress seem to increase from preadolescence to adolescence (2) and combine with inadequate coping, may induce stress’s well-known effects (3-5). Stress and mental health problems are strongly and significantly correlated for school students (6). Previous studies suggested that stress forms a non-specific risk factor for a wide range of mental health issues, behavioural problems and conduct disorders among adolescents (7-15). Adolescents who are stressed are at higher risk of a wide range of mental health conditions such as anxiety, depression (16), bipolar disorder (16), schizophrenia (16), eating disorders (17), personality disorders (16) and even suicide (18). Those mental health conditions were cited by adolescents as the second-most cited barriers to achieving study goals (19). High school students who experience negative affects and engage maladaptive coping are more likely have lower GPA (20). School related academic stress and burnout decreases student academic motivation and increases the risk for dropout (21, 22). Among adolescents, stress level is also associated with risky behaviours. Moderate- and high-level stress is associated with gaming addition among adolescents (23), and affects their family and social relationships, self-control and self-regulation, as well as academic performance (24, 25).

Managing stress among adolescents is considered to be critical to preventing mental health issues.

Previous studies have shown the benefits of delivering psychological interventions (26) in group formats for stress management among adolescents. In addition, developing countries, such as China, are lack of mental health professionals, especially school counsellors. Therefore, telehealth interventions (e.g., video conferencing, mobile apps etc.) might provide an option that reduce the demand of mental health professionals. In fact, telehealth interventions have been used for the management of adolescent mental health conditions such as anxiety, depression and stress previously. However, most of such interventions were conducted in western countries. Although two studies (27, 28) have transferred web-based self-help interventions (CATCH-IT and MoodGYM) to Chinese version and showed effectiveness among Chinese young people. However, the number is still very small (i.e., only 2 studies); besides, only Ip et al (27) conducted intervention in secondary school students with relatively large sample size. Ren et al (28) only tested the intervention with a sample of 62 among university student population. Little is known about the effectiveness of web-based interventions in Chinese adolescent context.

### Comparators

The comparator will be no treatment condition. This means that the control group will not be given the intervention product (a web-based stress managing website or an app).

## Objectives

This study aims to test whether an online school-based intervention for stress management is feasible, acceptable and effective among Chinese high school students. We hypothesise that our intervention (compared to the control group) will result in lower stress.

## Trial design

A superiority, two-arm, cluster randomized controlled trial will be conducted (see Figure 1 for the flow chart of the trial design). Confirmed participants will be randomly allocated in a 1:1 ratio into one of the study groups. In the intervention group, the participants will use an online stress-managing program which will be delivered via smartphone. Participants in the control group will not use the online program duration. However, they will be notified that they will have access to the online program after 12 weeks (i.e., at the end of the study). The condition to which each participant will be allocated will not be blinded for either experimenters or participants.

[figure not shown]

Figure 1 Flow chat of the trial design

# Methods

## Participants, interventions, and outcomes

### Study setting

This study will be conducted in two high schools: Mianyang Dongchen International School (MDIS) and Mianyang Nanshan High School (MNHS) in Mianyang City, Sichuan Province in China. MDIS is a private school and MHS is a public school.

### Eligibility criteria

Eligible participants include those (i) who will be enrolled in grade 10 and 11 at the beginning of the intervention; (ii) who own a smartphone and are allowed to use the smartphone during intervention period; Participants will be excluded if they (i) are intellectually impaired; (ii) are diagnosed with mental illness; (iii) are having medications which affect their mental health status (e.g., antidepressant) or attend regular counselling sessions.

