### Interventions

The intervention group will download a stress-managing app, the app can be used on mobile devices including mobile phones and tablets etc. The app will be based on Stress Inoculation Training (SIT) developed by Meichenbaum (29). Even though SIT was designed for military settings, there has been a lot of studies which adapted the SIT and use it among students and adolescents (30-34) and delivered SIT via technologies (35). Our study will modify SIT to high school context by adding assertiveness and training participants cognitive and behavioural techniques to deal with stressors arising from academic environment and peer interpersonal relationships. The online stress-managing intervention will comprise of 11 sessions which consist of psychoeducation, problem assessments, training of stress coping skills (emotion-focused coping skills and problem-focused coping skills), cognitive restructuring, imagery and behavioural rehearsal and role play (see [Appendix 1](#_Appendix_1) for details of the intervention content). The intervention content will be in Chinese language. The control group will not be given access to the app until the termination of the trial (12 weeks after the start of the trial). There will be no other intervention given to the control group. Both the intervention group and the control group will have full access to usual care, which is the psychological courses arranged by the high schools.

The criteria for discontinuing for a given trial participant include: (i) if they self-reported or reported by others to be suicidal; (ii) if they drop out of school during the intervention period; (iii) if they require to withdraw from the study.

Strategies to improve adherence to intervention protocol include:

- Instructions about the importance of following study guidelines for adherence to once weekly product.
- Instructions about the purpose and use of the intervention app.
- Notification sent via app weekly on each Sunday that there will be a session taken in the app.
- Successfully completion of each session will generate a virtual star in the participant’s account as a reward for the participation.
- Adherence assessments include log in times and other usage data collected in the app.

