Relevant concomitant care and interventions that are permitted or prohibited during the trial are as following: Both the intervention group and the control group will have full access to psychological courses as arranged according to the curriculums of the high schools. However, participants in either intervention group or control group will be prohibited to use psychological counselling services. Should they have any mental health conditions which require mental health assistance, they will be referred to relevant services AND the participants will be regarded as drop-outs.

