### Participant timeline

Table 1 and Figure 2 illustrate the time schedule of enrolment, randomization, interventions, and assessments for participants.

Table 1 Perceived Stress Reduction Protocol Schedule of Forms and Procedures

|  | | | **-1** | **T0** | **T1** | **T2** |
| --- | --- | --- | --- | --- | --- | --- |
| **Activity/**  **Assessment** | **Staff**  **Member** | **Approximate**  **Time to**  **Complete** | **Pre-Study**  **Screening/ Consent** | **Pre-Study**  **Baseline/**  **Randomization** | **Post-study**  **12 weeks** | **Follow-Up**  **16 weeks** |
| Consent Form | Head teachers | 20 Minutes | X |  |  |  |
| Inclusion/  Exclusion Form | Principal investigator | 5 minutes | X |  |  |  |
| Demographics Questionnaire | Principal investigator | 10 Minutes |  | X | X | X |
| PSS-10 | Principal investigator | 10 minutes |  | X | X | X |
| DASS-21 | Principal investigator | 20 minutes |  | X | X | X |
| ORS-4 | Principal investigator | 5 minutes |  | X | X | X |
| CISS-SFC | Principal investigator | 20 minutes |  | X | X | X |
| Randomization | Principal investigator | 15 Minutes |  | X |  |  |

[figure not shown]

Figure 2 Participant Timeline

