### Recruitment

Participants will be recruited from grade 10 and 11 at Mianyang Dongchen International School (MDIS) and Mianyang Nanshan High School (MNHS). MDIS has a student population of more than 2000 in grade 10 and 11. MHS has a student population of more than 3500 in grade 10 and 11. More than 90 percent of high school students (total n= 4950 students) in MDIS and MHS own a mobile phone, and both schools allow students to use mobile phones on the weekends. Recruitment strategies for the trial will involve posters, flyers, advertisement and announcements in class in those two schools. Students who are self-identified as feeling stressed will be recruited. For all participants, consent forms will be read and signed by themselves, their guardians and their head teachers.

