## Methods: Data collection, management and analysis

### Data collection methods

Data relating to perceived stress, negative mental health outcome, positive mental health outcome and coping behaviours will be collected at baseline (T0=0 weeks), post-intervention (T1=12 weeks) and follow-up (T2=16 weeks). Demographic data will only be collected at baseline (see Table1 for study variables). All data will be collected online via the mobile intervention app.

Baseline variables, including demographics, will be gather at the start of the study (Table 1).

Table 2 Study variables

| **Variable** | **Measure** |
| --- | --- |
| Demographic | Age |
|  | Gender |
|  | Grade |
|  | Home location (rural or urban) |
|  | Guardian (parents or others) |
| Perceived stress | PSS-10 |
| Negative mental health | DASS-21 |
| Positive mental health | ORS-4 |
| Coping Behaviors | CISS-SFC |

A description of study instruments along with their reliability and validity are provided below:

The Perceived Stress Scale-10 Items (PSS-10) is a ten item self-reported scale to assess respondents’ global level of perceived stress (36). Respondents were required to rate the frequency of certain feelings they experienced over the past month on a 5-point Likert Scale (1=never, 2=rarely, 3=sometimes, 4=often, 5=always). It has shown to predict the range of health-related outcomes presumed to be associated with appraised stress (36). PSS-10 is a shorter version of Perceived Stress Scale 14-item (PSS-14) that assesses how respondents perceives their lives to be unpredictable, uncontrollable and overloaded (48). The PSS-10 has been validated in populations in different countries and proven to possesses adequate internal consistency with Cronbach’s alpha coefficients ranging from 0.67 to 0.91 (49-54), moderate convergent validity with stressful life events (55), and good concurrent validity with mental health problems such as anxiety and depression (56-58). Particularly, the PSS-10 has been translated in Chinese and shown acceptable reliability and validity in both adults (37, 38) and adolescents (39).

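### Current suicidality ends participation but does not bar entry, and no question about it is described before randomisation

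*Protocol*

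**What the plan says.** The Protocol's Eligibility criteria give three exclusions: "Participants will be excluded if they (i) are intellectually impaired; (ii) are diagnosed with mental illness; (iii) are having medications", the last continuing to medicines that affect mental health and regular counselling. Suicidality is not named.

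Under Interventions, the first criterion for discontinuing a participant is "if they self-reported or reported by others to be suicidal". The Harms section lists suicidal ideation or attempts as a life-threatening condition. It counts them as a serious adverse event when the investigators believe the intervention caused them.

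On who is recruited, the Recruitment section states: "Students who are self-identified as feeling stressed will be recruited". The Background and rationale names, among the risks for stressed adolescents, "eating disorders (17), personality disorders (16) and even suicide (18").

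On care during the trial, Interventions states that "participants in either intervention group or control group will be prohibited to use psychological counselling services". If a need for mental health help emerges, "they will be referred to relevant services AND the participants will be regarded as drop-outs".

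Table 1 (Participant timeline) schedules two activities at the screening visit: consent, and a short eligibility form ("Exclusion Form | Principal investigator | 5 minutes"). The demographics questionnaire, the four scales and randomisation follow at T0. According to Data collection methods, the outcome data "will be collected at baseline (T0=0 weeks), post-intervention (T1=12 weeks) and follow-up (T2=16 weeks").

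**The concern.** The Protocol treats suicidality as serious enough to end participation, but does not treat it as a reason not to start. The second and third exclusions reach only students who already have a diagnosis, medication or counselling. A student who is suicidal but unknown to services passes all three.

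Enrolment also changes that student's position, because counselling services are then prohibited in both arms until someone reports a need. The referral rule does provide care once the need is known, so help is not withheld from a known case. The weakness is that nothing described in the Protocol seeks out the need at entry, which is the one planned moment before the restriction begins.

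A smaller issue concerns attribution of harms. The Harms section records all adverse events after entry, and reports those arising between consent and the start of the intervention as unrelated. What it cannot classify cleanly is suicidality that was present at entry but disclosed only after the intervention has begun.

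**Working it through.** The point rests on reading the sections against each other; no design figure is in dispute.

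**Step 1. Entry rule against stopping rule.**

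| Condition | Bars entry (Eligibility criteria) | Ends participation (Interventions) |
| --- | --- | --- |
| Intellectual impairment | Yes | Not listed |
| Diagnosed mental illness | Yes | Not listed by name |
| Relevant medication or regular counselling | Yes | Counselling is prohibited; a student needing help is referred and counted as a drop-out |
| Suicidal, by own or another's report | **No** | **Yes, first criterion** |

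Exclusions naming suicidality: 0 of 3.

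**Step 2. Is it asked before allocation?** Table 1 has 8 rows: consent, the eligibility form, demographics, PSS-10, DASS-21, ORS-4, CISS-SFC and randomisation. Two (consent and the eligibility form) fall at -1. Rows described as asking about suicidality: 0 of 8. The four scales are described as measuring perceived stress; depression, anxiety and stress; functioning; and coping. No rule is given for reviewing baseline answers or acting on them before allocation.

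**Step 3. When is the next scheduled look?** T1 − T0 = 12 − 0 = 12 weeks. Between the two, detection depends on an unscheduled report.

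**Step 4. Is such a student foreseeable?** Yes. Recruitment is aimed at students who feel stressed, and the Background links stress in adolescents to suicide.

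**Step 5. Would the extra exclusion harm the design?** First, the stated sample size. For d = 0.43, two-sided alpha 0.05 (two-sided is assumed) and power 0.80, the normal approximation gives 85 per arm. The t-test solution is 85.87, rounded up to 86 per arm, or 172 in total, as stated. Allowing for 10% drop-out, 86 / (1 − 0.10) = 95.6, so 96 per arm, or 192 in total, as stated. The planned total is 300.

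The Protocol gives no rate of suicidality. Assume that 1% to 10% of 300 would screen positive and not be replaced:

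| Assumed positive | Lost | Remaining | Power at d = 0.43 |
| --- | --- | --- | --- |
| 1% | 300 × 0.01 = 3 | 297 | 0.96 |
| 3% | 300 × 0.03 = 9 | 291 | 0.96 |
| 5% | 300 × 0.05 = 15 | 285 | 0.95 |
| 10% | 300 × 0.10 = 30 | 270 | 0.94 |

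Every row stays above 192. These powers ignore clustering by class, as the Protocol's own calculation does. They show only that the exclusion is affordable on the Protocol's own terms.

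**The case against.** The strongest reply is that an entry rule and a stopping rule need not mirror each other, so this is an omission and not a contradiction. The items on the eligibility form are also not shown and the consent pages were removed, so a question may exist there.

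The Protocol has several safeguards as well. The discontinuation rule applies to both arms and accepts reports from others. Anyone who needs help is referred. Adverse events are collected from consent. Guardians and head teachers sign consent. DASS-21, which covers depression, is completed at baseline. The intervention arm has weekly sessions with written feedback, a session on current problems, and help resources in the last session listed in Appendix 1.

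Part of this stands. It cannot be said that nobody asks, only that the Protocol describes no such question. The 12-week interval is less bare in the intervention arm than in the control arm. The remedy also catches only students who disclose, and asking minors about suicidality brings duties beyond one extra line on a form.

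The rest does not remove the gap. A screening form implements the written criteria, and those omit suicidality whatever the form contains. The discontinuation and referral rules act only after a report. No section says that the adults signing consent are asked, that baseline DASS-21 scores are reviewed, or that session feedback is read as a safety check; it is described as a measure of acceptance. Controls have no in-app sessions. The free counselling under Ancillary and post-trial care covers only distress caused by the intervention.

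**Conclusion.** The concern holds. As written, a suicidal student without a diagnosis, relevant medication or regular counselling is eligible and can be randomised into a trial that recruits for stress and prohibits counselling in both arms. The size can be given only as counts from the text: 0 of 3 exclusions, 0 of 8 scheduled activities, and 12 weeks to the next scheduled assessment. How many students this would affect is unknown.

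This is a safety improvement that should be made, not a statistical error; no bias in the primary comparison and no loss of power is claimed. Confidence is medium, because the conclusion assumes that the unseen eligibility form follows the written criteria.

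**What to change.** 1. Add a fourth exclusion under Eligibility criteria: *(iv) are currently suicidal, by self-report or report by others*. This matches the existing discontinuation criterion.
2. Add the corresponding item to the Inclusion/Exclusion Form at -1, completed before classes are randomised.
3. Name the principal investigator as the person who acts on a positive answer. Table 1 already assigns the form to that role, and Ancillary and post-trial care states that the role-holder is a registered psychological counsellor. The student is referred promptly (for example, the same day), before allocation, and is not enrolled.
4. State that the referral route under Interventions, now written for participants, also applies to students screened out, and say how guardians are told.
5. Keep the discontinuation criterion for suicidality that arises or is disclosed later.

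The cost is one eligibility line, one item on an existing 5-minute form, a short extension of the referral text, and the principal investigator's time to act on positive answers in two schools. A few students are excluded. No design figure changes.

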### Interventions

The intervention group will download a stress-managing app, the app can be used on mobile devices including mobile phones and tablets etc. The app will be based on Stress Inoculation Training (SIT) developed by Meichenbaum (29). Even though SIT was designed for military settings, there has been a lot of studies which adapted the SIT and use it among students and adolescents (30-34) and delivered SIT via technologies (35). Our study will modify SIT to high school context by adding assertiveness and training participants cognitive and behavioural techniques to deal with stressors arising from academic environment and peer interpersonal relationships. The online stress-managing intervention will comprise of 11 sessions which consist of psychoeducation, problem assessments, training of stress coping skills (emotion-focused coping skills and problem-focused coping skills), cognitive restructuring, imagery and behavioural rehearsal and role play (see [Appendix 1](#_Appendix_1) for details of the intervention content). The intervention content will be in Chinese language. The control group will not be given access to the app until the termination of the trial (12 weeks after the start of the trial). There will be no other intervention given to the control group. Both the intervention group and the control group will have full access to usual care, which is the psychological courses arranged by the high schools.

The criteria for discontinuing for a given trial participant include: (i) if they self-reported or reported by others to be suicidal; (ii) if they drop out of school during the intervention period; (iii) if they require to withdraw from the study.

Strategies to improve adherence to intervention protocol include:

- Instructions about the importance of following study guidelines for adherence to once weekly product.
- Instructions about the purpose and use of the intervention app.
- Notification sent via app weekly on each Sunday that there will be a session taken in the app.
- Successfully completion of each session will generate a virtual star in the participant’s account as a reward for the participation.
- Adherence assessments include log in times and other usage data collected in the app.

Relevant concomitant care and interventions that are permitted or prohibited during the trial are as following: Both the intervention group and the control group will have full access to psychological courses as arranged according to the curriculums of the high schools. However, participants in either intervention group or control group will be prohibited to use psychological counselling services. Should they have any mental health conditions which require mental health assistance, they will be referred to relevant services AND the participants will be regarded as drop-outs.

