### Sample size

According to a meta-analysis on internet interventions on stress reduction (45), which reported that the overall mean effect size for stress at posttest was Cohen d=0.43 (95% CI 0.31-0.54). Significant, small effects were found for depression (Cohen d=0.34, 95% CI 0.21-0.48) and anxiety (Cohen d=0.32, 95% CI 0.17-0.47). Following this meta-analysis, we therefore choose effect sizes of d=0.43 for perceived stress, d=0.34 for depression and d=0.32 for anxiety. An absolutely reduction of 4.03 points is chosen as minimum clinically significant difference according to a previous study that analyzed PSS-10 scores in terms of minimum clinically significant important difference (MCID) (46). Based on this expected difference, no expected PSS-10 change in the control group, a population mean PSS-10 of 13.7 (SD=5.6) equal between groups (47), a sample size of 172 (n=86 in each study group) is required to detect effect size of d=0.43 with a power (1− β) of 0.80 with alpha of 0.05. A sample size of 192 (n=96 in each study group) will be needed when allowing for 10% drop out. Considering the availability of target sample, we will choose a sample size of 300 (n=150 for each study group).

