### Statistical methods

Statistical analyses will be performed using SPSS 22.0 (SPSS Inc., Chicago, IL). We will present descriptive data in a table: categorical variables (e.g., gender, grade, home location etc.) will be presented as counts and percentages. Continuous variables (e.g., age, PSS-10, DASS-21, ORS-4 etc.) will be presented as mean and standard deviation (SD).

To determine whether any significant differences exist between intervention group and control group at baseline, independent t test will be conducted on continuous baseline variables (e.g., age, PSS-10, DASS-21, ORS-4, CISS-SFC, MER), and chi-square analyses will be conducted on categorical or nominal variables (e.g., gender, home location, guardian etc.).

To determine whether the intervention is effective, intention-to-treat (ITT) analyses will be conducted separately (59). The ITT analysis will include the data from the whole randomized sample. A linear mixed model (LMM) will be used to investigate the effects of time and groups on the primary outcome variables. The LMM will be performed with group, time, and group × time as fixed effects. Subjects and schools will be selected as random effects in order to take into consideration both within-subject and within-school correlations. Cohen d effect sizes will be calculated to examine the magnitude of between-group differences. Similar analyses will be conducted for exploring effects on secondary outcome measures.

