### Harms

In our study an adverse event will be defined as serious psychological distress experienced by participants without regard to the possibility of a causal relationship. Adverse events will be collected after the subject has provided consent and enrolled in the study. If a subject experiences an adverse event after the informed consent document is signed but the subject has not started to receive study intervention, the event will be reported as not related to study intervention. All adverse events occurring after entry into the study will be recorded. If an adverse event meets the criteria for a serious adverse event after study enrolment, this will be reported to Centre for Online Health, The University of Queensland. If the participant drop out as a result of an adverse event, study personnel will document the circumstances and data leading to discontinuation of the intervention. A serious adverse event for this study is any occurrence that is believed by the investigators to be causally related to the intervention and results in any of the following: Life-threatening condition (i.e., suicidal ideation or attempts), hospitalization due to mental health conditions, drop out of school.

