### Ancillary and post-trial care

Participants who suffer from psychological distress as a result of the intervention will receive free counselling from the principal investigator (XZ). The principal investigator is a registered psychological counsellor in China, XZ is also experienced with conducting individual and group psychotherapy with adolescents and school students.

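### Students referred for mental health help are classed as drop-outs without separating stopping the app from leaving follow-up, so their 12- and 16-week PSS-10 may go uncollected; the likely bias is small

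*Protocol*

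**What the plan says.** Under Interventions, counselling services are barred in both arms during the trial. Students who come to need mental health assistance are handled by one rule: "they will be referred to relevant services AND the participants will be regarded as drop-outs". The same section lists criteria for discontinuing a participant, the first being "i) if they self-reported or reported by others to be suicidal". It does not say whether the app, the assessments or both are discontinued.

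Four other places bear on how these rules would be applied:

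- Sample size raises 172 to 192, the number that "will be needed when allowing for 10% drop out".
- Statistical methods states "The ITT analysis will include the data from the whole randomized sample".
- Harms says that when a participant drops out because of an adverse event, "study personnel will document the circumstances and data leading to discontinuation of the intervention".
- Ancillary and post-trial care adds a counselling offer for those who suffer "distress as a result of the intervention will receive free counselling".

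The PSS-10 is scheduled at weeks 0, 12 and 16 only. No section says that a student classed as a drop-out is still asked for the week-12 and week-16 questionnaires.

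**The concern.** Needing mental health help is closely related to perceived stress, which is the primary outcome. If staff take the drop-out label at face value, a student referred before week 12 stays in the randomised sample with a baseline PSS-10 and nothing else. The intention-to-treat sentence governs who is analysed; it cannot supply values that nobody collected. A mixed model corrects only the part of the loss that observed scores predict, and for an early referral that means baseline alone.

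This is a rule of conduct. An analysis plan can choose a missing-data method but cannot recover an uncollected week-12 score. The trial recruits students who describe themselves as stressed, so some referrals are plausible. The eligibility exclusions (diagnosed mental illness, medication affecting mental health, regular counselling) should keep them few.

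The trial is open, so referral could differ by arm. Counselling for distress caused by the app is one conceivable source, since controls cannot have such distress before week 12. The protocol does not say when that counselling is given or whether it makes the student a drop-out.

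**Working it through.** **1. What drop-out means in the plan's own arithmetic.** A two-sample t-test with d = 0.43, two-sided alpha 0.05 and power 0.80 needs 85.87, so 86 per arm (172). Allowing for 10% drop-out, 86 / (1 − 0.10) = 95.6, so 96 per arm (192). Both figures reproduce. Dividing by 0.90 makes sense only if a drop-out gives no week-12 value.

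**2. What is lost.** Referral between weeks 0 and 12 leaves T0 only. Referral between weeks 12 and 16 leaves T0 and T1, so the primary comparison keeps that student.

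**3. Inputs for the size.**

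- From Sample size: d = 0.43, SD 5.6, 150 per arm.
- Assumed, because the documents give no figure: correlation between PSS-10 visits r = 0.5–0.7; correlation of the referral trigger with week-12 stress c = 0.5–0.7; 5% or 10% of controls referred, all before week 12; the same distress threshold k in both arms. Class and school effects are left out.

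**4. Formula.** Work in SD units and write λ(k) = φ(k)/Φ(k). After baseline is used, the uncorrected shift in an arm's week-12 mean is about w·λ(k).

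- If the trigger tracks only week-12 stress, w = c(1 − r²).
- If the trigger is equally correlated with baseline and week-12 stress, w = c(1 − r).

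An effective app lowers the trigger by s, where s = 0.43c in the first case and 0.43c/(1 + r) in the second. Dilution ≈ w·[λ(k) − λ(k + s)].

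**5. True d = 0.43.**

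- Upper end (10% of controls, c = 0.7, r = 0.5, week-12 stress only): k = 1.282, λ = 0.195; s = 0.301, λ(1.583) = 0.121; w = 0.7 × 0.75 = 0.525. Dilution = 0.525 × 0.074 = 0.039.
- Lower end (5% of controls, c = 0.5, r = 0.7, both visits): k = 1.645, λ = 0.109; s = 0.43 × 0.5 / 1.7 = 0.126, λ(1.771) = 0.086; w = 0.5 × 0.3 = 0.15. Dilution = 0.15 × 0.022 = 0.003.

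Simulating the planned type of model (random intercept; group, time and their interaction; 2,000,000 students per arm) agrees closely:

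| Trigger | 5% of controls | 10% of controls |
|---|---|---|
| Week-12 stress only | 0.009–0.025 d | 0.014–0.040 d |
| Baseline and week-12 equally | from about 0.004 d | up to about 0.023 d |

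The overall range is 0.004–0.04 d, or 0.004 × 5.6 = 0.02 to 0.04 × 5.6 = 0.22 points. If only half the referrals fall before week 12, the first row shrinks to 0.004–0.018 d across both referral rates.

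**6. No true effect.** With equal referral s = 0, the two λ terms cancel and the bias is about zero. At 8% versus 4%, λ = 0.162 and 0.090, a difference of 0.072. Multiplying by w from 0.15 to 0.525 gives 0.011–0.038, so about 0.01–0.04 d (0.06–0.22 points). It favours the app if the app arm loses more students and goes against it if controls do.

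**7. Scale.** At r = 0.5 the standard error of the difference in change at 150 per arm is √(2/150) = 0.115, so the largest shift is 0.04 / 0.115 = 0.35 of a standard error. Power without clustering falls from 96% to 91% at worst in these scenarios. The protocol's own minimum important difference is 4.03 points.

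**The case against.** The strongest reply is that this rests on a reading. Nothing in the protocol ends data collection for drop-outs. The visit schedule makes no exception for them, and the Harms section links drop-out to stopping the intervention, which fits the view that a drop-out merely leaves the programme. The 10% allowance is generic and does not mention referral. All of this is correct. A reader might infer that the protocol orders questionnaires to stop, and the documents do not support that. What stands is that drop-out carries two senses, neither is said to govern follow-up, and the intention-to-treat sentence concerns analysis and does not instruct anyone to keep collecting.

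The second reply is that the effect is negligible: a few hundredths of d, with assumed referral rates. The upper figures also need a trigger that follows week-12 stress alone. A trigger that also reflects baseline stress brings the dilution to about 0.004–0.023 d. This stands too, and it sets the priority.

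Third, unequal referral is conjecture, since one rule covers both arms. That is fair. The app-distress counselling shows only that imbalance is possible.

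**Conclusion.** The point holds as an ambiguity in a conduct rule with a small expected effect. On the ordinary reading of drop-out, the week-12 and week-16 PSS-10 of referred or suicidal students would not be collected, for a reason tied to the outcome and against the stated intention-to-treat aim.

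Under the assumptions above, dilution at a true d of 0.43 is about 0.004–0.04 d: the lower half if the trigger is also correlated with baseline stress, the upper end if it tracks week-12 stress alone. With no true effect the bias is about zero under equal referral, and 0.01–0.04 d in either direction at 8% versus 4%. The real referral rate, its timing and any imbalance are unknown.

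A reader might infer that the rule threatens the trial's conclusion or systematically flatters the app. The figures do not support the first, and no stated fact fixes a direction for the second. The change is worth making because the lost values are irrecoverable and the remedy is cheap, so it ranks as an optional improvement.

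**What to change.** Amend the discontinuation and concomitant-care paragraphs under Interventions to say:

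- Referral for mental health help, or discontinuation for safety, ends the app sessions only.
- Unless consent is withdrawn or contact is clinically inappropriate, these students are still asked for the 12- and 16-week questionnaires.
- They are analysed in the arm of their randomised class, and referrals are reported by arm with timing.
- Counselling under Ancillary and post-trial care is handled the same way.

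The referral and safety rules themselves stay as they are. The estimate will then include any effect of care received after referral, which fits the intention-to-treat aim.

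The cost is a short amendment approved by both ethics bodies, a few more questionnaires, and a clinical check before contacting students discontinued as suicidal. A questionnaire route without the sessions is also needed. The trial needs one for controls anyway, because "All data will be collected online via the mobile intervention app" while "The control group will not be given access to the app until the termination of the trial", but the protocol does not describe it. Some of the most distressed students may still go unmeasured, so the gain is partial.
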